### Data collection

Informed consent will be sought from all participants prior to enrollment. The health-center-level baseline data will be collected from all 16 clusters, by health center coordinators using an environmental assessment checklist, prior to the start of the intervention. The same tool will be used throughout intervention implementation and at the conclusion of activities. World Health Organization guidelines indicate that a simple checklist to assess infection prevention control practice, using key indicators, can provide important information for process monitoring and evaluation [17]. Individual-level data related to the outcomes noted above, including primary, secondary, and exploratory outcomes, will be collected through interview by VHSG project coordinators during enrollment in the third trimester of participant’s pregnancy, and on the 14th and 29th day of newborn life, at the household level.

Midwives will provide mothers with a referral form at the time of discharge of the newborn from the health center (the day after birth), in case the infant is subsequently brought to the hospital for any reason. The form will alert hospital staff to collect a blood culture on arrival for infants presenting with possible infectious diseases prior to administering antibiotics. Infants under one month of age presenting to facility with signs of sepsis, based on the definitions given by Zaidi *et al*. [12], will have blood samples taken for culture and assayed at Takeo hospital laboratory.

### Sample size and power calculation(s)

Using all-cause newborn mortality as the exploratory outcome and a stepped wedge design for cluster randomized trials, we would require a total sample size of 1,957, based on 80 % power, a 5 % significance level, and a 10 % rate of loss-to-follow-up, to detect a 20 % reduction in neonatal mortality with a baseline of up to 40 deaths per 1,000 live births at the provincial level. For this study, health centers with an expected minimum of 20 births per month will be included, resulting in a study population of at least 320 per month, or 5,540 participants over one year and five months. This will allow us to meet more than 80 % power of the study primary objectives. Secondary analyses will examine the impact through process indicators based on a smaller sample. Other intervention phase outcomes with higher baseline rates than all-cause mortality (incidence of newborns with specific danger signs and proportion of newborns with danger signs referred to an appropriate facility) are hypothesized to demonstrate 20 % or greater improved outcome in the intervention group, but the lack of reliable baseline data on these does not allow us to use them for power calculations.

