## Background

While global estimates of newborn mortality have been declining, it remains an important public health problem in low income countries, particularly in settings where under five-year-old and maternal mortality rates have decreased more rapidly [1, 2]. It is estimated that up to 40 % of global under five-year-old mortality occurs in the newborn period (during the first 28 days after birth) [3]. In Cambodia, maternal and under five-year-old mortality rates have been significantly reduced over the last 10 years, falling from 472 per 100,000 live births in 2005 to 206 per 100,000 live births in 2010, and 83 per 1,000 live births in 2005 to 54 per 1,000 live births in 2010, respectively. Newborn mortality, however, has been more difficult to address at 28 per 1,000 live births and 27 per 1,000 live births in 2005 and 2010 [4, 5].

In order to address the continued newborn mortality burden, the Cambodian Ministry of Health (MoH), under the guidance of the Prime Minister, resolved to redouble efforts to achieve significant progress in reducing newborn mortality at its Annual Congress in 2011. Attendees at the Annual Health Congress, including the United States Agency for International Development (USAID), the National Reproductive Health Program, and key non-governmental organizations (NGOs) and United Nations partners were called upon and agreed to work with the MoH in reducing high newborn and child mortality rates in Cambodia. As yet, however, there has been no agreed national strategy on how best to achieve the called-for reductions.

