#### Exploratory outcomes

The exploratory outcomes for the study are as follows: all-cause newborn mortality, and cause- and age-specific newborn mortality. While our study may not be sufficiently powered to show reductions in mortality, we anticipate that if the hypothesis above is sustained with larger populations, the intervention will be associated with a reduction in all-cause mortality, and more specifically, in infection-associated mortality.

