### Trial design

The health center functions as the unit of allocation, with health centers randomized to an intervention start date using a stepped wedge design. The design is principally a matched one, with before and after comparisons for each unit of randomization. On the hypothesis that 16 health centers are recruited, one health center will be assigned to start each month, and randomization will be stratified in order to ensure balance across time points. In this design, all clusters (health centers) receive the intervention in due course (unidirectional crossover) and, in particular, the intervention is never removed once it has been implemented, which allows convenience and alleviates ethical concerns. All cases will be used in the primary analysis, constituting an intent-to-treat approach. Full study enrollment will be completed at 16 months and duration of participation in the intervention will vary based on randomization assignment, with all clusters enrolled with a unidirectional approach and participating for the last six months of the trial.

All health centers in the trial will be included in the intervention, but will be randomized to one of 16 start dates. The center-level intervention will be implemented one stage at a time, progressively over the study period, until all centers have received the intervention. In addition to center level, patient-level data will also be collected. Thus the analysis is divided into center level and patient level, with the patient-level analysis as the primary outcome. All live births occurring in the study area will be eligible, and pregnant women in the last trimester will be recruited from health center catchment areas using the stepped wedge design, where each area will serve initially as control and later as intervention. The study will enroll a target sample size of 1,957 recently delivered women.

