### Analysis plan

The analyses of study data will be performed using the principle of intention-to-treat for the analysis of randomized controlled trials. The exploratory data analysis will be performed for all descriptive statistics, such as means, proportions, variances, and correlation by time and group. Two group (control and intervention) comparison analysis at each time point, across all time points and within each cluster will be performed. One-way crossover design analysis methods will be used for stepped wedge design data, that is, analyses will be performed accounting for potential within-cluster correlation using a random effect model, multilevel model, or generalized estimating equations. Based on each month of the study, we will compare the neonatal mortality rate in those centers that have not yet received the intervention with those in the centers that have. The study hypothesis will be tested on the significance level of alpha = 5 % throughout the analysis. All analyses, summaries, listing, and graphing will be performed on the data, using SAS software (version 9.1 or higher in a Windows environment SAS Institute Inc. Cary, North Carolina, USA). In order to avoid the potential problem of multiple comparisons related to the primary outcomes we plan to apply a Bonferroni correction.

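### 1,957 women do not give 80% power for a 20% fall in neonatal mortality: power is about 9–15%, and the required number is roughly ten or more times larger

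*Protocol article*

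**What the plan says.** The section on sample size and power states "we would require a total sample size of 1,957". Its assumptions are 80% power, alpha of 5% and one participant in ten lost. The effect sought is a fall of one fifth, and the starting rate is taken as no more than 40 per 1,000 in the province. The same figure is the recruitment target under Trial design: "The study will enroll a target sample size of 1,957 recently delivered women".

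The sample-size section then expects at least 320 births a month, which it totals as 5,540 over 17 months, and says this gives more than 80% power for the primary objectives. It adds that other outcomes could not be used for power calculations because reliable baseline data are lacking.

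Three other places bear on the point:

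- Exploratory outcomes lists mortality as exploratory and warns that "our study may not be sufficiently powered to show reductions in mortality".
- Background gives national newborn mortality as "28 per 1,000 live births and 27 per 1,000 live births in 2005 and 2010".
- The Analysis plan compares neonatal mortality month by month between centers with and without the intervention, and says "The study hypothesis will be tested on the significance level of alpha = 5 % throughout the analysis".

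**The concern.** A 20% relative fall from 4% is an absolute difference of 0.8 percentage points in a rare event. With fewer than 2,000 newborns, only about 35 deaths against 28 would be expected in two equal halves. No ordinary comparison separates those counts with 80% power.

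The figure carries weight. It is the article's only formal sample-size calculation, it fixes the enrolment target, and it is the only quantitative support for the claim of adequate power on the primary objectives. A reader who takes the 80% at face value could treat a null mortality result as evidence against the package, although the study would usually miss a true 20% fall.

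**Working it through.** **Inputs from the article.** Baseline 0.040. A 20% reduction, read as relative, gives 0.032 (a 20-point absolute fall from 4% is impossible). Alpha 5%, taken as two-sided because sidedness is not stated. Power 80%, loss 10%. There are 16 health centers with one crossing over each month, over 17 months. **Not given:** ICC and women per center-month.

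**1. Reproducing 1,957, ignoring clustering and time.**

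n per group = (1.96 + 0.842)² × (0.04 × 0.96 + 0.032 × 0.968) / 0.008² = 7.849 × 0.069376 / 0.000064 = 8,508.

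The total is 2 × 8,508 = 17,016, and 17,016 / 0.9 = 18,907 with loss. The ratio to the stated figure is 18,907 / 1,957 = 9.7.

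Variants do not recover 1,957:

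| Variant | Total before loss |
|---|---|
| Pooled variance | 17,022 |
| Continuity-corrected | 17,520 |
| One-sided 5% | 13,408 |
| One-sample test against a fixed 4%, two-sided | 4,426 |
| One-sample test against a fixed 4%, one-sided | 3,458 |

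**2. Power with the stated number, ignoring clustering.** Evaluable: 1,957 × 0.9 = 1,761, or 880.5 per half.

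SE = √(0.069376 / 880.5) = 0.00888, and 0.008 / 0.00888 = 0.901.

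Power = Φ(0.901 − 1.96) + Φ(−0.901 − 1.96) = 14.7%. Using all 1,957 gives about 16%. One-sided testing of all 1,957 gives at most 24%. With 1,761, 80% power is reached only for a reduction of about 56%.

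**3. Stepped wedge.** Standard variance with a random center effect and fixed month effects, I = 16, T = 17:

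Var = Iσ²(σ² + Tτ²) / [(IU − W)σ² + (U² + ITU − TW − IV)τ²]

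Here U = 136 and W = V = 1,496, so IU − W = 680 and the τ² coefficient is 6,120. Women per cell: 1,761 / (16 × 17) = 6.47. Individual variance: 0.036 × 0.964 = 0.0347.

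At ICC 0: σ² = 0.0347 / 6.47 = 0.00536; Var = 16 × 0.00536 / 680 = 0.000126; SE = 0.0112; 0.008 / 0.0112 = 0.71; power 11.0%.

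| Assumed ICC | SE | Power, 1,761 evaluable | Enrolment for 80% power, with 10% loss |
|---|---|---|---|
| 0 | 0.0112 | 11.0% | about 30,300 |
| 0.01 | 0.0129 | 9.5% | about 55,100 |
| 0.05 | 0.0141 | 8.7% | about 54,000 |
| 0.2 | 0.0136 | 9.1% | about 45,700 |

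Layouts of 16 or 22 periods give 8.3–11.4%. Without month effects, power is about 13–15% over the same ICC range. Even at ICC 0.5 the required enrolment stays above 28,000.

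**4. The larger population.** 320 × 17 = 5,440 (the article prints 5,540). Less 10%, that is 4,896 newborns: power 32% ignoring clustering and 15–22% in the stepped wedge. All 5,540 with no loss: 36% and about 16–24%.

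**5. A lower baseline.** At 27 per 1,000 (national, 2010) the contrast is 27 with 21.6. The plain comparison needs 12,760 per group, 25,519 in total before loss. Power with 1,761 is about 11% ignoring clustering and 7–9% in the stepped wedge.

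**Possible source (conjecture).** 17,016 × 0.1035 / 0.9 = 1,957. A stepped-wedge design effect near 0.10 may therefore have been applied as if it gave the trial total. That type of formula gives the number per measurement period, to be multiplied by 17 when each newborn is counted once. At ICC 0 it gives 1,602 × 17 = 27,234, in line with step 3 before loss. The article states no ICC or design effect, so this cannot be confirmed, and nothing here depends on it.

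**The case against.** Mortality is exploratory, none of the six primary outcomes is mortality, and the article itself warns of low power for it. That limits the harm: a careful reader of the Exploratory outcomes section would not over-interpret a null result, and nothing above shows that a primary outcome is underpowered. It does not make the sample-size statement true. One section says 80% power is reached with 1,957 women, the other says power may be insufficient, and the enrolment target rests on the first.

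The stepped-wedge figures depend on an assumed ICC, on month effects the Analysis plan does not spell out, and on a 17-month layout. This stands, so they are given as ranges. The 14.7% uses only the article's inputs and a two-sided test.

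The 27 per 1,000 is national, whereas the 40 is described as provincial. This also stands: 27 is a sensitivity value, not a contradiction. The 40 is nonetheless worded as an upper bound, and the claim fails there too.

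If every birth is analysed, the miss rate is lower than nine in ten. This is correct: with 4,896 evaluable it is about 68–85%. Power is still far below 80%.

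**Conclusion.** The statement is wrong as written. For 40 against 32 per 1,000 at two-sided 5%, 1,957 women with 10% loss give 14.7% power with no clustering at all. A 16-center stepped wedge with month effects gives about 9–11% for ICC 0 to 0.2. On 1,957 women the study would therefore miss a true 20% fall about 85–91% of the time. The number needed is 18,907 on the most favourable two-sided two-group calculation, and about 30,000 to 55,000 in the stepped wedge for the ICCs considered. No sidedness, ICC, layout or population figure tried brings the stated number near 80% power. The claim also conflicts with the article's own caution under Exploratory outcomes.

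**What to change.** - Delete the claim of 80% power for mortality from the sample-size section.
- State instead what 1,957 women (about 1,761 evaluable) provide: about 15% power for a 20% fall from 40 per 1,000 ignoring clustering, about 9–11% in the stepped wedge with month effects, and less at a lower baseline. Replace the assumed ICC range with the investigators' own value, and give the period layout and women per center-month used.
- Align this text with Exploratory outcomes, and report mortality as an estimate with a confidence interval rather than as a powered test.
- Do not infer more than 80% power for the primary objectives from the mortality calculation. Keep 1,957 as the planned enrolment if that is the intention, say plainly that it was not derived from a valid mortality calculation, and show the precision it gives on the primary outcomes over a range of assumed baseline proportions and ICCs.

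The cost is protocol wording and a short recalculation. No extra participants are needed. The stated power becomes much less favourable.

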### Outcomes

#### Primary outcomes

The primary outcomes for the study are as follows:Percentage of mothers who know at least three danger signs;Percentage of VHSG volunteers who know six danger signs;Percentage of families who seek care from an appropriate facility;Decreased time between onset of suspected danger signs and referral to appropriate facility;Improved infection prevention behaviors by family, as measured by the proportion of hand washing with soap at key events, calculated as a composite score from the percentage of mothers or caretakers reporting hand washing at the following key events: after going to toilet, before touching newborn, before eating, and after cleaning baby’s bottom;Improved infection prevention and control behavior among health center staff, as measured by the proportion of appropriate hand washing with soap or disinfectant at key points in provision of care to mothers and newborns, calculated as a composite score from: percentage of health center staff reporting hand washing: before patient contact (when they examine mother and newborn), before and after aseptic procedure, after exposure to blood or body fluids, after patient contact (after removing gloves), and after touching patient surroundings.

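### The stated power of more than 80% for the primary objectives is unsupported for every primary outcome and takes no account of the Bonferroni level or the outcomes' own denominators

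*Protocol article*

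**What the plan says.** All references are to the protocol article.

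- **Sample size and power calculation(s).** The calculation is introduced with "Using all-cause newborn mortality as the exploratory outcome and a stepped wedge design for cluster randomized trials". The total it arrives at is 1,957, using 80% power, a 5% level and an allowance of 10% for loss. The target effect is worded as "to detect a 20 % reduction in neonatal mortality with a baseline of up to 40 deaths per 1,000 live births". The paragraph then expects at least 320 births a month, 5,540 participants over 17 months, and says this gives more than 80% "power of the study primary objectives".
- **Same paragraph.** Two other outcomes, the incidence of danger signs and the proportion of newborns with danger signs who are referred appropriately, are expected to improve by 20% or more. For them, "the lack of reliable baseline data on these does not allow us to use them for power calculations".
- **Primary outcomes.** Six are listed: mothers' knowledge of danger signs, volunteers' knowledge of danger signs, "Percentage of families who seek care from an appropriate facility", time from onset of danger signs to referral, family hand washing, and staff hand washing.
- **Exploratory outcomes.** Mortality is placed here, with a warning that the study may lack power for it.
- **Trial design.** "The study will enroll a target sample size of 1,957 recently delivered women".
- **Analysis plan.** A Bonferroni correction is to be applied for the primary outcomes.

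**The concern.** A stated power is a property on which readers of the result will rely. Here it is asserted for the primary objectives, but the one calculation shown belongs to a different, exploratory outcome and uses an alpha that the primary outcomes will not be tested at. The paragraph also says that power could not be calculated for an outcome close to two of the six. The count of births cannot serve as the denominator for outcomes measured on volunteers, on staff, or only on newborns with danger signs.

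The trial is meant to inform national policy. If care-seeking or referral time shows no significant change, the result would be read against a power above 80% for which the article gives no basis, and uncertainty could be taken for absence of effect.

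**Working it through.** **1. The plan's own figure.** Inputs: 40 against 32 per 1,000, 80% power, 5% (two-sided assumed), 10% loss. Per group, without clustering:

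n = [1.960·√(2·0.036·0.964) + 0.842·√(0.04·0.96 + 0.032·0.968)]² / 0.008² ≈ 8,511

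The total is 17,022, or 17,022/0.9 = 18,914 after loss. The stated 1,957 is not reproduced. One-sided testing (13,408 before loss) and a stepped-wedge variance with month effects (about 25,650 or more even at ICC 0) do not give it either. The mortality calculation therefore cannot stand in for the missing ones.

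**2. Alpha.** 0.05/6 = 0.00833, so the critical value rises from 1.960 to 2.638. An outcome with exactly 80% power at 5% has effect/SE = 1.960 + 0.842 = 2.802. At the corrected level its power is Φ(2.802 − 2.638) = Φ(0.164), about 56%. This step needs no assumed baseline or ICC.

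**3. Sample sizes.** Enrolment target: 1,957 × 0.9 = 1,761 evaluable. Expected births: 16 centers × 20 = 320 a month; 320 × 17 = 5,440 (the article prints 5,540); 5,440 × 0.9 = 4,896 evaluable.

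**4. Outcomes measured in all mothers, 20% read as relative.** Assumptions that the article does not supply: the baselines, ICC 0.02 to 0.05, and the use of the 20% improvement for these outcomes. Model: 16 clusters × 17 months, month effects, random cluster effect. Total variance is s² = m(1 − m), with m = 1.1 × baseline; the cluster variance is ICC·s²; the residual variance of a cell mean is (1 − ICC)·s²/(N/272). The SE comes from generalized least squares, and power = Φ(Δ/SE − 2.638).

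| Evaluable | Baseline | Δ | SE (ICC 0.02; 0.05) | Power at 0.83% |
|---|---|---|---|---|
| 1,761 | 30% | 0.06 | 0.0342; 0.0357 | 17–19% |
| 1,761 | 50% | 0.10 | 0.0362; 0.0378 | 50–55% |
| 4,896 | 30% | 0.06 | 0.0218; 0.0222 | 53–54% |
| 4,896 | 40% | 0.08 | 0.0230; 0.0234 | 78–80% |
| 4,896 | 50% | 0.10 | 0.0231; 0.0235 | about 95% |

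Example, first row at ICC 0.02: 0.06/0.0342 = 1.754; Φ(1.754 − 2.638) = Φ(−0.884) ≈ 0.19. At an uncorrected 5%, the two rows with 1,761 give 39–42% and 75–79%.

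**5. The same outcomes, 20% read as percentage points.** With Δ = 0.20 and m = baseline + 0.10, power at 0.83% is above 99% at both sizes for every baseline from 10% to 75%.

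**6. Care-seeking, if limited to newborns with danger signs.** Assumed share 20%, baseline 50%, ICC 0.02. Denominators: 0.2 × 1,761 = 352 and 0.2 × 4,896 = 979.

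| Newborns | Relative (Δ = 0.10) | Percentage points (Δ = 0.20) |
|---|---|---|
| 352 | Φ(0.10/0.0719 − 2.638) = 11% | Φ(0.20/0.0708 − 2.638) ≈ 58% |
| 979 | Φ(0.10/0.0463 − 2.638) = 32% | Φ(0.20/0.0456 − 2.638) ≈ 96% |

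**7. Not computable.** The article gives no number of volunteers or staff. Time to referral is not a proportion, and the hand-washing outcomes are composite scores without a stated variance. The figures above apply to binary outcomes such as mothers' knowledge.

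**The case against.** Four points on the other side have force.

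- A journal article is condensed, and a calculation for the primary outcomes may exist elsewhere. That stands as far as it goes: the article shows none, which does not prove that none was made. But the article makes the claim itself and undercuts it in the same paragraph, so this is more than detail left to another document.
- The statement about missing baselines covers two named outcomes only. It does not say that knowledge or hand washing could not be powered. That also stands; for those outcomes the point is only that no support is shown.
- The power sentence follows the 5,540 figure, not 1,957. Figures for the smaller number alone would therefore be unfair, and both are given.
- The 20% is a minimum, is not labelled relative or absolute, and is not stated for mothers' knowledge or hand washing. Read as percentage points, it reverses the picture for all-mother outcomes.

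A reader might infer that the trial falls short of 80% power over most plausible baselines. The documents do not support that. They give no baselines from which to judge what is plausible. With 4,896 evaluable and a 20% relative effect at 0.83%, 8 of 15 baselines between 10% and 80% (in steps of 5 points) reach 80% for an all-mother outcome.

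**Conclusion.** The statement of more than 80% power for the primary objectives is unsupported for every primary outcome as the article stands. That conclusion rests on the text alone, as does the omission of the Bonferroni level, which takes an outcome with exactly 80% power at 5% down to about 56%.

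The size of any shortfall is conditional. Under an assumed 20% relative improvement, all-mother outcomes miss 80% at low to moderate baselines: at 30% with either sample size, and still at 50% with 1,761 evaluable. From about 41% upward, 4,896 evaluable is enough at ICC 0.05. Under a 20-point improvement these outcomes are well powered throughout. Care-seeking is the more exposed: three of its four scenarios fall below 80%. They rest on an assumed 20% share of newborns with danger signs and on the inference, which the outcome list does not state, that only those newborns count. For volunteers, staff and time to referral nothing can be computed, so a power above 80% can be neither confirmed nor refuted.

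**What to change.** - Delete the claim of more than 80% power for the primary objectives.
- Put in its place a short table of the minimum detectable difference for each of the six primary outcomes at 0.05/6. Each should use its own denominator (all mothers, newborns with danger signs, volunteers, staff), over stated ranges of baseline and ICC.
- Base the table on the sample size that will actually be enrolled, after reconciling 1,957 with 5,540.
- State whether the hypothesized 20% is relative or absolute, and to which outcomes it applies.
- Data from the early control months can supply baselines without any comparison between conditions.

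The cost is one table and a less favourable statement of power. No extra participants are needed, and no outcome or analysis method changes.
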